## Abstract

Background: Minimally invasive heart valve surgery via anterolateral mini-thoracotomy with full endoscopic 3D visualization (MIS) has become the standard treatment of patients with valvular heart disease and low operative risk over the past two decades. It requires extracorporeal circulation and cardioplegic arrest. The most established form of arterial cannulation for MIS is through the femoral artery and is used by most surgeons, but it is suspected to increase the risk of stroke through retrograde blood flow. An alternative route of cannulation is the axillary artery, producing antegrade blood flow during extracorporeal circulation. Methods: Femoral or axillary cannulation for extracorporeal circulation during minimally invasive heart valve surgery (FAMI) is a multicenter randomized controlled trial designed to determine whether axillary cannulation is superior to femoral cannulation for the outcome of a manifest stroke within 7 days postoperatively. The target sample size was 848 participants. Patients ≥ 18 years of age, with valvular regurgitation or stenosis scheduled for minimally invasive surgery via anterolateral mini-thoracotomy, were randomized to axillary cannulation (treatment group) or to femoral cannulation (standard care). Patients were followed up for seven days postoperatively. A CT scan was performed pre-operatively to screen patients for vascular calcifications and to assess the safety of femoral cannulation. The standard of care is femoral artery cannulation, but is performed only in patients without significant vascular calcifications or severe kinking of the iliac arteries and in patients with sufficient vessel diameter. The cannulation is performed via Seldinger’s technique, and the vessel closed percutaneously using a plug-based vascular closure device. Only patients without significant vascular calcifications are considered for femoral cannulation, as an increased risk of stroke is assumed. In patients with vascular calcifications, axillary cannulation is the standard of care to avoid these risks. Retrospective studies have hinted that, even in patients without vascular calcifications, there may be a lower stroke risk with axillary cannulation compared to femoral cannulation. We present a protocol for a multi-center randomized trial to investigate this hypothesis. Discussion: To date, evidence on the best access for peripheral artery cannulation during minimally invasive heart valve surgery has been scarce. Patients may benefit from axillary cannulation for extracorporeal circulation in terms of stroke risk and other neurological and vascular complications, though femoral cannulation is the gold standard. The aim of this study is to determine the risks of peri-operative stroke in a prospective randomized comparison of femoral vs. axillary cannulation.

## 1. Introduction

### 1.1. Background

Minimally invasive heart valve surgery via anterolateral mini-thoracotomy with full endoscopic 3D visualization (MIS) has become the standard treatment for patients with valvular heart disease and low operative risk in experienced centers in Europe over the past two decades. Compared to conventional median sternotomy, this surgical technique has been shown to have a low postoperative complication rate in terms of postoperative pain, length of ICU stay (including length of postoperative ventilation), and overall length of hospital stay [1,2].

In minimally invasive heart valve surgery, the heart–lung machine for extracorporeal circulation is usually not connected (hence “cannulated”) centrally to the ascending aorta, but via peripheral vessels. Extracorporeal circulation is needed for the induction of cardiac arrest and opening the cardiac chambers to enable valve replacement or valve reconstruction.

The most established form of cannulation for MIS is via the femoral artery. This is considered a safe cannulation route in patients without significant vascular calcifications, which can be seen in routine pre-operative computed tomography (CT) scans. An alternative cannulation route is through the axillary artery. In order to use this access, an exposure of the vessel is required, which is more time-consuming compared to femoral cannulation and most often requires an additional small surgical incision below the clavicular bone, as Seldinger’s technique is less preferred. Retrospective studies suggest an increased stroke risk with femoral cannulation, even in patients without significant vascular calcifications [3,4]. This is explained by the concept of “retrograde” and “antegrade” perfusion in the aorta during cardiopulmonary bypass and cardioplegic arrest (see Figure 1), which provides a possibility of mobilizing calcium and debris upward to the supraaortic vessels. Significant kinking or stenosis may also lead to hypoperfusion proximally or may carry a risk of vessel injury during cannulation. 

### 1.2. Objectives

The aim of this study was to determine the risks of peri-operative stroke in a prospective randomized comparison of femoral vs. axillary cannulation in minimally invasive heart valve surgery.

### 1.3. Trial Design

This trial is planned as a multi-center, randomized, prospective, controlled trial to achieve data of the highest scientific quality. The study data will be collected and managed using REDCap electronic data capture tools hosted at Vanderbilt University [5,6]. A blinding for the investigator and patient is evidently not possible. Mock-incisions are considered as unethical; thus single-blinding is also not possible. Stroke and disability are endpoints which will be assessed through objective measures (CT scans, NIH Stroke Scale, Modified Rankin scale). The trial will be performed following all legal requirements and scientific standards, especially the Good Clinical Practice (GCP) guideline, including onsite and remote monitoring of the data, adequate training of the staff, standardized safety management, and quality management of the trial.

### 1.4. Methods

#### Study Settings Pre-Operatively

Patients with heart valve disease (aortic, and/or tricuspid, and/or mitral) with indication for surgery will receive a CT-scan, performed pre-operatively to prepare patients and assess the safety of femoral and axillary cannulation. A recent meta-analysis suggested a reduced risk of stroke in minimally invasive heart valve surgery using pre-operative CT scans [7].

For screening purposes, a special CT angiography is carried out from neck to groin. It is carried out using a contrast agent, and imaging is ECG-triggered. In addition, a reconstruction is shown in a coronary sectional plane (see Figure 2). CT screening is routinely applied in all MIS patients and may show accidental findings that are contraindicative to femoral cannulation. In cases of severe renal impairment, the need for a contrast agent may be waived; however, it is preferable to obtain CT images using a contrast agent. 

### 1.5. Eligibility Criteria

Patients with valvular insufficiency or stenosis who are planned for minimally invasive surgery via anterolateral mini-thoracotomy, as well as patients who are suitable for both femoral and axillary cannulation using the heart–lung machine according to their CT scan (i.e., no relevant calcifications of the pelvic leg vessels and the aorta, sufficient vessel diameter (see Figure 2)) are eligible for enrolment. 

Patients with vascular access sites that are anatomically unsuitable for femoral or axillary artery cannulation, vascular calcifications, or higher-grade stenoses in the supra-aortic vessels, or patients with pre-interventional complications at the vascular access site (before the actual minimally invasive valve replacement/reconstruction procedure), are not eligible. 

Inclusion criteria: Patients with valvular regurgitation or stenosis scheduled for minimally invasive surgery via anterolateral mini-thoracotomy. Patients suitable for both femoral and axillary cannulation of the heart–lung machine (i.e., no relevant calcifications of the iliac leg vessels and the aorta, sufficient vascular diameter). Consent of the patient after detailed explanation of the study. Age of patient: >18 years old.

Exclusion criteria: A vascular access site that is anatomically unsuitable for cannulation in the femoral or axillary artery. Patients with vascular calcifications, higher-grade stenoses in the para-aortic vessels, pre-interventional complications at the vascular access site (before the actual minimally invasive valve replacement/reconstruction procedure), unstable active bleeding, bleeding diathesis, or significant unmanageable anemia also inhibit the capacity of the patient to give consent. 

### 1.6. Surgical Procedure Step-by-Step

At the beginning of the procedure, the patient is fully heparinized (400 I.E. Heparine/kg body weight). Successful heparinization is measured using “Activated clotting time”, which should exceed 450 s and be monitored repeatedly. Extracorporeal circulation (ECC) is established percutaneously via femoral vessels under transesophageal echocardiography (TEE) guidance. Alternatively, cannulation of the axillary artery after cut-down in the infraclavicular groove or under ultrasound guidance via Seldinger’s technique can be performed. The arterial cannula diameter ranges from 16 to 20 Fr, and is needed for the generation of enough flow through extracorporeal circulation at outlet pressures below 300 mmHg. 

We perform the procedure in normothermia; however, if need be, mild hypothermia may be applied. Venous cannulation always includes femoral access in cases of >80 kgs of body weight or tricuspid valve surgery, and an additional venous neck cannula may be placed through the internal jugular vein. 

Then, a right thoracotomy is performed through 2nd or 3rd intercostal space over approximately 5 cm. Access through the ribs is needed during apnea, as well as disconnection of the endotracheal tube. A soft tissue retractor is used and a 3D optic is inserted through a port one intercostal space above the thoracotomy incision. Continuous inflation of CO_2_ via the endoscopy port is applied. The pericardium is opened above the phrenic nerve, and stay sutures are placed for visualization. 

Separation of the aorta from the pulmonary artery, release of the adhesions on the aorta, and insertion of the transthoracic aortic clamp via another stab incision craniolateral from the surgical incision are performed. Vents are placed on the ascending aorta and, in cases of aortic valve surgery, the right upper pulmonary vein. Cross-clamping of the aorta and administration of 1500–2000 mL of crystalloid cardioplegia solution via the aortic root are carried out. If aortic valve (AV) regurgitation is severe, cardioplegia may be administered directly into the ostia. 

In cases of aortic valve surgery, after the induction of sufficient cardioplegia, the aorta is incised transversally. Then, the aortic valve procedure, repair, or replacement is performed as needed. Afterwards, control of the coronary ostia and control of the leaflets, then double row closure of the aorta, are performedIn cases of mitral valve surgery, a retraction suture is placed at the level of the right atrium to expose the interatrial grove. The left atrium is then opened at the level of the interatrial grove and exposed using a retractor, which is stabilized by another stab incision, parasternal at the level of the same intercostal space used for thoracotomy (see Figure 3). Then, the mitral valve procedure, repair, or replacement is performed as needed. Afterwards, the waterprobe of the left atrium is closed using continuous double layered sutures.

Placement of a temporary pacemaker electrode to the right ventricle is necessary before releasing the aortic cross clamp. Next, a de-airing maneuver is performed (recruitment of ventilation and temporarily reducing venous drainage with strong suction on the left ventricular vent as well as at the aortic vent). The aortic cross-clamp is released. 

After sufficient reperfusion, ventilation is initiated and establishment of a stable rhythm occurs, then extracorporeal circulation is weaned gradually and terminated. The venous line may be decannulated using one deep skin suture and manual compression of the vessel. The arterial femoral line is decannulated using the MANTA percutaneous vascular closure system (Teleflex, Morrisville, NC, USA).

In cases of axillary cannulation, the arterial line is removed and previously-placed purse string sutures are tied down. The vessel is inspected for any complications (stenosis dissection, etc.), and afterward, the axillary wound may be closed (3–4 cm). Heparin is antagonized using Protamine. The surgical incision, pleura, and pericardium are inspected for any signs of bleeding.

Two chest drains are routinely placed through the same incisions used for the endoscope and the aortic clamp, one pleural drain and one pericardial drain. The ribs are adapted using a thick suture to prevent lung hernia. After that, the wound is closed in a layered fashion. Incisions may be infiltrated with local anesthetics and the patient may be extubated on the operating table directly afterwards, which is routine at out center. Figure 1 shows the operative setup of MIS with surgical incisions and possible cannulation sites.

## 2. Outcomes 

### 2.1. Primary Endpoint

Manifest stroke (confirmed by imaging or non-transient new neurological deficit) can occur within 7 days postoperatively.

### 2.2. Secondary Endpoints

Rate of transient ischemic attacks;Modified Rankin Scale (0–6 points) at discharge;Rate of postoperative delirium (mean CAM-ICU score);Neurological status assessed by mean NIH Stroke Scale at discharge;Rate of seizures generalized and focal;Hours on ventilator post-procedure;Long-term survival rate (1 year);Rate of access-site or access-related bleeding;Rate of wound healing disorders in the cannulation area;Rate of iatrogenic aortic dissection;Thromboembolic events of limbs;Rate of pseudoaneurysm or other vascular complications at access site.

## 3. Study Visits

The study will be conducted at high-volume heart valve centers specializing in MIS with >250 minimally invasive heart valve procedures performed annually per center. All patients admitted for minimally-invasive valve surgery at the participating centers will be screened and assessed for eligibility. CT scans will be performed as per the standard of care, and consent will be obtained after the CT scans show eligibility for both cannulation routes. The course of study is listed in Table 1. The modified Rankin scale (mrs) and NIH stroke scale are routinely assessed as per the protocol outlined in Table 1. The mrs measures the degree of disability after a stroke, and the NIH stroke scale quantifies the stroke’s severity. The members of the study team performing these assessments must obtain a training certificate prior to performing assessments on the study patients. 

### 3.1. Provisions for Post-Trial Care

There will be no compensation for patients since both procedures are well established and there is no off-label-use. No additional insurance for participating patients is needed as the cannulas for the heart–lung machine are used within the scope of their instructions for use, and the cannulation strategy in itself is not experimental.

### 3.2. Sample Size and Statistical Analysis

The assumed stroke rate in the intervention group is 1%, and in the control group 4%, based on reported outcomes from a propensity-matched retrospective study of both techniques consisting of >1500 patients [3,4] (Murzi et al. [3,4]. Based on our calculations, 424 patients per group must be included (i.e., 848 patients in total) to test the primary endpoint with a power of 80%. Overall, we assumed a slightly lower stroke rate in the control group than previously reported (4% instead of 5%) to ensure enrolment of enough patients to achieve sufficient power to test the primary endpoint if the stroke rate turns out to be lower. 

The efficacy of the primary endpoint will be calculated using the chi-square test. The endpoint will be measured and tested using the stroke rate up to 7 days postoperatively in both groups. All other categorical endpoints will be measured using chi-square tests. Secondary endpoints with continuous variables will be compared using the t-test for comparison of means, Kaplan–Meier for survival (log-rank) and chi-square for categorical endpoints. A combined endpoint may be created, consisting of stroke, delirium, and access-site-related complications at 30 days to further assess overall safety of the cannulation routes and to achieve a higher level of sensitivity in detecting complications by both treatments.

An interim analysis will be performed after inclusion of 50% of the patients (424). If a significantly higher stroke rate is shown in one group which exceeds the expected stroke rate, the trial may be stopped and concluded for safety reasons and obvious superiority of one technique. If the actual stroke rate differs from the assumed stroke rate, sample size calculation may be repeated on the basis of interim analysis, and enrolment will be adjusted accordingly.

A study flow-chart detailing the screening, enrolment, and study process can be seen in Figure 4.

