**Figure 4 jcm-12-05344-f004:**
[figure not shown]
FAMI study flow-chart detailing the screening, enrolment, and study process.

**Table 1 jcm-12-05344-t001:** Course of FAMI study.

	Course of Study			
	Inclusion	Reference	Visits	
Time	-t1 (Pre-OP)	t0 (Intra-OP)	t1–3: Post-OP	t7 or Date of Discharge: Follow Up
**Screening**	X	X		
**Informed consent**	X			
**Clinical examination**	X	X	X	X
**CT-angiography**	X		X *	X *
**Modified Rankin Scale**	X		X	X
**NIH Stroke scale**	X		X	X
**CAM-ICU**			X	X

* Cranial CT is only performed postoperatively if the patient presents with neurological symptoms.

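### The delirium endpoint is called a rate but defined as a mean score, and the NIH Stroke Scale comparison at discharge leaves the scheduled pre-operative value unused

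*Protocol article*

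**What the plan says.** Section 2.2 of the protocol article gives three neurological secondary endpoints that matter here:

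- delirium: "Rate of postoperative delirium (mean CAM-ICU score";
- stroke severity: "Neurological status assessed by mean NIH Stroke Scale at discharge";
- disability: "Modified Rankin Scale (0–6 points) at discharge", with no summary measure named.

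Section 3.2 assigns the tests. For continuous endpoints, "Secondary endpoints with continuous variables will be compared using the t-test for comparison of means". For the rest, "All other categorical endpoints will be measured using chi-square tests". No covariate is named. The same section mentions delirium as one component of a possible combined endpoint, beside stroke and access-site complications. The Discussion (section 7) reports delirium from a retrospective study of 1280 patients as 14% versus 5%.

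Section 3 states that "The modified Rankin scale (mrs) and NIH stroke scale are routinely assessed as per the protocol outlined in Table 1". Table 1 marks both of those scales pre-operatively, at t1–3, and at t7 or discharge. CAM-ICU is marked only at t1–3 and at t7 or discharge, with no pre-operative assessment.

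**The concern.** There are two separate points.

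**Delirium.** A rate is a proportion of patients and a mean score is an average of a measurement. The line in section 2.2 names both, and section 3.2 sends them to different tests. Two analysts following the text could report different quantities, and the choice could be made after the data are seen. CAM-ICU is scheduled at more than one post-operative time, and the article does not say how repeated assessments are combined or what the mean is taken over.

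**NIH Stroke Scale.** The endpoint is the discharge mean and the test is an unadjusted t-test. A pre-operative value is scheduled for every patient but has no stated role in the comparison. If some patients enter with deficits, that between-patient variation stays in the error term although the data to remove it are already being collected.

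These endpoints would be read closely if the comparison of a rare primary event turned out inconclusive.

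**Working it through.** **1. The plan's own figure.** Inputs from section 3.2: 4% versus 1%, power 80%. Alpha is not stated; two-sided 0.05 is assumed. With pooled variance under the null and mean rate 0.025:

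n = [1.960 × √(2 × 0.025 × 0.975) + 0.842 × √(0.04 × 0.96 + 0.01 × 0.99)]² / 0.03² = 423.97, that is 424 per group.

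The stated 424 is reproduced. Neither point below enters this calculation.

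**2. Delirium, place by place.**

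| Place | Delirium is |
|---|---|
| Section 2.2, before the bracket | a rate |
| Section 2.2, in the bracket | a mean score |
| Section 3.2, combined endpoint | an event |
| Section 7, cited study | a percentage (14% vs 5%) |

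Three of the four need a yes/no status per patient. The bracket agrees with them only if each patient contributes a single value coded 0 or 1, because the mean of such values is the proportion. The article does not say this, and Table 1 schedules repeated assessments. For illustration, assume four assessments coded 0/1 and averaged within patient: a patient positive once contributes 1/4 = 0.25 to the mean but 1 to the rate.

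With the per-patient proportion, the cited rates of 14% and 5%, 424 per group and two-sided 0.05 (mean rate 0.095):

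- standard error under the null: √(2 × 0.095 × 0.905 / 424) = 0.0201;
- standard error under the alternative: √[(0.14 × 0.86 + 0.05 × 0.95) / 424] = 0.0199;
- power = Φ[(0.09 − 1.960 × 0.0201) / 0.0199] = 0.994.

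So if the cited difference applied here, the trial could show it clearly, provided the endpoint is defined.

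**3. Baseline adjustment.** With correlation ρ between the pre-operative and discharge values, adjustment multiplies the residual variance by 1 − ρ². The detectable standardised difference at 80% power is (1.960 + 0.842) × √[2(1 − ρ²)/424], and the equivalent unadjusted sample size is 424/(1 − ρ²). The documents do not give ρ, so a range is shown.

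| Assumed ρ | Variance cut | Detectable difference (SD) | Equivalent n per group |
|---|---|---|---|
| 0 (no gain) | 0% | 0.192 | 424 |
| 0.3 | 9% | 0.184 | 466 |
| 0.5 | 25% | 0.167 | 565 |
| 0.7 | 49% | 0.137 | 831 |

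**4. Check with mostly-zero scores.** 4,000 simulated trials per setting, 424 per group, stroke 4% versus 1%, and an assumed mean score of 6 in patients with stroke, added to any pre-operative score.

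| Assumed pre-operative scores | Power, t-test | Power, ANCOVA |
|---|---|---|
| all zero | 0.79 | nothing to adjust for |
| 5% non-zero, mean 2 (ρ about 0.44) | 0.68 | 0.79 |
| 10% non-zero, mean 3 (ρ about 0.71) | 0.46 | 0.78 |

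With equal stroke rates in both groups, the unadjusted t-test rejected in 4.0% to 5.3% of trials at a nominal 5%.

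**The case against.** The strongest defence is that the unadjusted t-test is not an error. Randomisation makes it unbiased, and it kept its type I error in the simulation. Choice of covariates is normal content for an analysis plan that is not shown. Eligibility excludes vascular calcification and higher-grade stenoses, so pre-operative NIH Stroke Scale scores may be almost all zero, and then there is nothing to gain. All of this stands, and it limits the second point to an inexpensive improvement of unknown size. It does not touch the delirium line, which the article itself states inconsistently.

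A reader might infer more than the text supports:

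- *That these outcomes are uninterpretable.* The NIH Stroke Scale comparison is valid. Only delirium has an unclear estimand.
- *That the modified Rankin Scale is compared as a mean.* Section 2.2 gives only its range and timing, and section 3.2 does not say whether it counts as continuous or categorical.
- *That a rank or proportional-odds analysis is clearly better.* With non-zero scores assumed uniform from 1 to 20 and stroke at 1% versus 4%, a rank test had power of about 0.83 against 0.72 for the t-test. But a chi-square test on any non-zero score also had 0.83 and agreed with the rank test in 99.8% of trials, so the gain largely repeats the primary stroke comparison. With 4% stroke in both groups but scores of 1–5 against 10–20, the t-test had power 0.96 and the rank test 0.05. Proportional odds is a preference, not a correction.
- *That deaths before discharge drop out of the mean.* The article does not say how they are handled, and this can be left to the analysis plan.

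**Conclusion.** The point holds in two parts of unequal weight.

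The delirium definition contradicts itself and conflicts with the event and percentage used elsewhere in the article. This needs no assumption and should be corrected.

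The missing baseline adjustment costs precision only. The loss runs from close to nothing to roughly half the variance (49% at ρ = 0.7), depending on a correlation that the documents do not give. It concerns the two scales scheduled pre-operatively (NIH Stroke Scale and modified Rankin Scale), not CAM-ICU.

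Both parts concern secondary endpoints. The primary chi-square comparison and the 424 per group stand as they are.

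**What to change.** 1. In section 2.2, replace the delirium line with: the proportion of patients with at least one positive CAM-ICU across the scheduled post-operative assessments (t1–3 and t7 or discharge). Compare by chi-square and report the risk difference with a 95% CI. Use the same event for delirium in the combined endpoint if that is created.
2. In section 3.2, state that the discharge comparisons of the NIH Stroke Scale and the modified Rankin Scale are adjusted for the pre-operative value, for example ANCOVA for the NIH Stroke Scale. State also which summary measure and test apply to the modified Rankin Scale.

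The cost is wording in the protocol or analysis plan, settled before outcome data are examined by group. Table 1 already schedules every assessment needed, and neither the sample size nor the visits change.

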## 4. Data Management

In this study, the randomization of patients assigned to different interventions was conducted using an online randomization tool. The use of such a tool ensures a fair and unbiased allocation of participants to the intervention groups. The randomization process involved assigning each participant a unique identifier and then using the online tool to generate a random sequence of assignments. This method helps to minimize selection bias and ensures that each participant has an equal chance of being assigned to any of the intervention groups. The online randomization tool used in this study provides a transparent and efficient way to allocate participants, enhancing the validity and reliability of the research findings. By employing this randomization method, we aim to ensure the integrity and rigor of our study design.

A simple randomization process was performed using the REDCap database in this study. The purpose of the randomization was to assign participants to different treatment groups in a completely unbiased manner. Therefore, we used the simple randomization application. This method ensures that each participant has an equal chance of being assigned to any of the treatment groups, minimizing potential biases and increasing the reliability of the study results. The randomization process was conducted using the REDCap database, which provides a secure and efficient platform for data management in research studies.

The data will be stored on a secure server in the protected environment of the Study Centre Bonn. A full-time data manager is already employed by our department and is familiar with data export to REDCap. Data handling will be conducted in accordance with the GCP guidelines and current European data legislation. A GCP-compliant eCRF with secured access and an implemented audit trial will be used. Central monitoring with plausibility checks, as well as on-site monitoring, will be implemented following a risk-adapted approach to ensure high data quality. After clearance and final analysis of the data, as well as the publication of study results, the data will be made publicly available.

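### Ventilator hours are compared by a t-test with no centre term, which may lose precision if extubation practice differs between centres

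*Protocol article*

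**What the plan says.** Section 2.2 of the protocol article lists "Hours on ventilator post-procedure" among twelve secondary endpoints. Section 3.2 names the test for endpoints of this kind: "Secondary endpoints with continuous variables will be compared using the t-test for comparison of means". It mentions no centre term and no stratified comparison.

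Section 1.3 describes the design: "This trial is planned as a multi-center, randomized, prospective, controlled trial". The number of centres is not given. On allocation, section 4 says: "A simple randomization process was performed using the REDCap database in this study". No stratification by centre is stated.

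The end of section 1.6 says that "the patient may be extubated on the operating table directly afterwards, which is routine at out center". That is the only statement on extubation. It is permissive, it ties the routine to one centre, and no section describes practice elsewhere.

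**The concern.** Where on-table extubation is routine, most patients should have close to zero ventilator hours after the procedure, whichever artery is cannulated. If other participating centres usually extubate later, much of the spread in ventilator hours would come from where the patient was operated on rather than from the cannulation route. A two-sample t-test puts that spread into its error term.

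Centre is known for every patient and fixed before treatment, so the variation can be removed without bias. At stake is the width of the confidence interval for one secondary endpoint, and the chance of detecting a real difference in ventilation time.

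**Working it through.** **The plan's own figure.** The only sample size in the article is for stroke: "424 patients per group must be included (i.e., 848 patients in total", at 80% power, with assumed rates of 4% and 1%. Two-sided alpha 0.05 is not stated; I assume it because it reproduces the figure. With the pooled-variance formula and mean rate 0.025:

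- 1.960 × √(2 × 0.025 × 0.975) = 0.4327
- 0.8416 × √(0.04 × 0.96 + 0.01 × 0.99) = 0.1850
- n = (0.4327 + 0.1850)² / 0.03² ≈ 424 per group

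This matches, and nothing below changes it. No power target is stated for ventilator hours.

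**Inputs for ventilator hours.** The article gives no mean, SD, between-centre variance or split of patients by centre. All of these are assumptions:

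- w, the share of patients in centres that extubate on the table: 0.25 to 0.75
- those centres: mean 0.3 h, SD 1.5 h
- the other centres: mean m = 4 to 10 h, SD s = 6 to 10 h

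**Formulas.**

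- Within-centre variance W = w × 1.5² + (1 − w) × s²
- Between-centre variance B = w(1 − w)(m − 0.3)²
- Share of variance due to centre = B / (W + B)
- Patient-equivalent ratio = (W + B) / W
- Fall in standard error from adjusting = 1 − √(W / (W + B))

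**Results.**

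| Case | w | m | s | W | B | Centre share | Ratio | SE falls by |
|---|---|---|---|---|---|---|---|---|
| Lowest | 0.25 | 4 | 10 | 75.56 | 2.57 | 3% | 1.03 | 1.7% |
| Middle | 0.50 | 6 | 6 | 19.13 | 8.12 | 30% | 1.42 | 16% |
| Highest | 0.75 | 10 | 6 | 10.69 | 17.64 | 62% | 2.65 | 39% |
| Same practice everywhere | – | – | – | – | 0 | 0% | 1.00 | 0% |

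Within the assumed ranges, the first and third rows are the true extremes.

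**In terms of power.** Take an effect that a centre-adjusted analysis would detect with 80% power at 424 per group. The unadjusted t-test's standard error is larger by 1/√(1 − centre share):

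| Centre share of variance | SE multiplied by | Power of the unadjusted t-test |
|---|---|---|
| 0 | 1.00 | 80% |
| 0.10 | 1.05 | 76% |
| 0.20 | 1.12 | 71% |
| 0.30 | 1.20 | 65% |
| 0.50 | 1.41 | 51% |

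**Type I error.** I used a simulation with 848 patients, five assumed centres, simple randomisation and 4000 runs. At centre shares of 0, 0.2 and 0.4, the unadjusted test rejected a true null hypothesis in 5.1%, 5.7% and 4.9% of runs. Its power was 80%, 71% and 59%, against about 80% throughout for the centre-adjusted analysis. So the loss is in power, not in false positives.

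**The case against.** The strongest objection is that the premise is not in the document. No section says that any other centre extubates differently. Section 3 describes all sites as high-volume centres specialising in this surgery, with more than 250 such procedures a year. That does not show equal extubation practice, but it means that a contrast cannot be taken as fact. This stands: the point has to be conditional, and a gain of nothing is within its range.

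Second, the size is wholly assumed. This also stands. At the low end of the assumed range the gain is under 2% of the standard error.

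Third, centre adjustment is often left to the analysis plan or full protocol, neither of which is shown. This stands only in part. The article does not leave the analysis open: it names a specific test for these endpoints, and that test has no centre term. The point is about that stated choice, not about missing detail.

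Fourth, the t-test is valid under simple randomisation, and ventilator hours is one of twelve secondary endpoints. Both are true. The proposal improves efficiency and does not repair an invalid method.

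A reader might infer more: that pooling centres biases the comparison, or that it raises the false-positive rate. Neither follows. Patients are randomised individually with an equal chance of either arm, and the simulated type I error is near 5%. Nor do the documents support the reading that centres are known to differ.

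**Conclusion.** The point holds in conditional form. Section 3.2 fixes an unadjusted t-test for ventilator hours in a multicentre trial, and the article itself identifies a centre practice that bears directly on that endpoint. If extubation practice differs between centres, precision is lost that one model term would recover.

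Under the assumptions stated above, adjustment is worth between 1.03 and 2.65 times the patients for this endpoint, with 1.42 in the middle case. If practice is alike everywhere it is worth about 1.00. The document cannot say where in this range the trial lies.

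This is a low-cost improvement to one secondary endpoint. The stroke analysis and the 848 patients are not affected.

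**What to change.** In section 3.2, replace the t-test for ventilator hours with a linear model containing treatment and centre, with robust standard errors, and report the adjusted difference in means with its confidence interval. The reported effect remains a difference in mean hours.

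The cost is one line of wording and a few degrees of freedom out of about 846 (848 − 2). If centres turn out to be alike, almost nothing is lost. No extra data are needed beyond each patient's centre, and neither randomisation nor clinical practice changes. Section 8 reports that the trial is still enrolling, so the change can be made before the final analysis.
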